### Analyses

The primary outcome measure of caries experience for this study will be the differences in mean dmfs measures for the children in the two treatment arms at ages one, two, and three. Descriptive analyses (frequencies, means, and standard deviations) will be performed first in order to guide the statistical analyses. Longitudinal methods of analysis will be used to examine these repeated and correlated observations within subjects over time. Exploratory analysis will first be done to evaluate the trends in the data in order to determine the most appropriate mean and covariance structures to fit the data. Graphic displays will be used to assess the mean structure for modeling fixed effects, including scatter plots of the response variable versus time, plots of individual subject profiles and plots of mean profiles. Linear mixed models will be used to fit the data. Once a suitable covariance structure has been determined, an appropriate means structure will be determined. The mean structure might be linear or nonlinear over time and each of these will be tested.

Secondary outcomes will include caries patterns, oral health knowledge and behavior and cost analyses. Caries patterns will be analyzed by looking at dmfs components according to specific teeth in the mouth. A cost analysis will be conducted and will relate the cost of the intervention to the results of the study. To facilitate this, data regarding the time required for each aspect of the study will be periodically collected. This will allow for the analysis of personnel costs associated with the intervention. The costs of all enhanced community service efforts will also be readily available for analysis once the study is complete.

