### Intervention

#### Motivational interviewing (MI)

A culturally specific MI script was developed with a Native MI consultant, a training manual was compiled, intervention providers were trained, and a pilot test was completed before the MI intervention was used in the field. The intervention providers are local people with some education beyond high school, no oral health training or experience but with experience working in a position with public interaction. The two day training for the intervention providers includes MI material written by the Native MI expert with emphasis on integrating AI and western practices providing the foundation for MI with AI populations
[28]. They learn and demonstrate the use of communication skills to work with people as partners as they consider personal behavior change. They practice fundamental MI techniques that focus on helping clients strengthen the motivation to improve oral health behaviors. During training, the intervention providers conduct five audio-recorded practice sessions of mothers or caregivers for review and feedback by the MI intervention director in consultation with the MI consultant. Once the intervention providers are fully trained they will start intervention visits. However, every intervention will be recorded and a fidelity measurement will be conducted (discussed below).

Participants will choose the location where they meet with the MI intervention provider. A participant may choose to meet at their home, in a common public place (such as a local library in a private room), at the field office, or another community program location. Whenever possible, the same intervention provider will meet with the same study participant for each of the four interventions. At each MI intervention visit, the date of the visit, age of the child, content selected for discussion, the mother or caregiver’s decisions regarding next steps, their satisfaction with the visit, and oral health supplies left with the family will be recorded. The MI intervention providers will also record missed visits and all attempts to schedule visits.

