### Sample size

Based on the IHS 1999 dental survey of the AI population
[1], the mean dmfs for all AI nationally was 10.05 (SD = 16.27) at age two and 12.22 (SD = 19.17) at age three. Assuming a repeated measures analysis with dmfs measured at 3 time points (years one, two and three), an intra-class correlation of 0.50, a 40% reduction in mean dmfs due to the MI intervention, a 90% statistical power using an α = 0.05 2-sided test, and an 80% retention rate, we arrived at a total sample size of 540 mothers and newborns in the two treatment arms (270 per arm). The final target sample size was set at 600 to allow for some potential misspecifications of the statistical assumptions.

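### Neither the sample size nor the described analysis allows for variation between MI providers, so the MI-versus-control interval will be too narrow if outcomes differ by provider

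*Protocol article*

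**What the plan says.** Under Analyses, the protocol article compares mean dmfs between arms at ages one, two and three with linear mixed models. The correlation it describes is within the child: "Longitudinal methods of analysis will be used to examine these repeated and correlated observations within subjects over time". The covariance structure is to be chosen after exploratory work, which consists of plots against time and of individual and mean profiles.

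Under Sample size, the inputs are a mean dmfs of "10.05 (SD = 16.27) at age two and 12.22 (SD = 19.17) at age three", "a 40% reduction in mean dmfs due to the MI intervention", three yearly measurements, "an intra-class correlation of 0.50" and "a 90% statistical power using an α = 0.05 2-sided test, and an 80% retention rate". The result is 270 per arm, 540 in total. The target was then raised to 600 as a general margin for wrong assumptions.

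Under Motivational interviewing (MI), sessions are delivered by trained local lay providers, and "Whenever possible, the same intervention provider will meet with the same study participant for each of the four interventions". Measurement of fidelity adds that 20% of recordings are scored for adherence and competence, with feedback to the provider. Randomization is of individual mothers or caregivers, stratified by caregiver age. Study design gives both arms the same number of visits. The article does not give the number of MI providers or say who conducts the control visits.

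**The concern.** With individual randomization, the usual case for treating children as independent is sound until treatment starts. From then on, children whose mothers see the same provider may share whatever that provider does well or badly. The protocol intends this grouping by asking for continuity, and its fidelity monitoring allows that providers may differ in skill. Variation between providers adds to the variance of the MI-arm mean, and a larger number of children per provider does not average it away. A model with correlation only within children leaves that variance out. The interval for the MI effect is then too narrow, and the trial has less power than stated. The 0.50 in the sample size does not cover this: it describes repeated measurements on one child, not different children of one provider.

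**Working it through.** **Inputs from the document (Sample size):** age-three mean 12.22, SD 19.17; reduction 40%; within-child ICC 0.50; three visits; two-sided 5% level; 90% power; 80% retention; 600 enrolled.

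**Assumptions, not in the document:** k = 4 to 12 providers, equal caseloads, provider ICC ρ of 0.01, 0.02 or 0.05 on the scale of the child's mean over visits, and no provider component in the control arm.

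**Step 1: reproduce 540.**
- Difference: 0.40 × 12.22 = 4.888 surfaces.
- Variance of a child's mean over three visits: 19.17² × (1 + 2 × 0.50)/3 = 244.99, so SD 15.65.
- Evaluable per arm: 2 × 244.99 × (1.960 + 1.282)² / 4.888² = 215.5, rounded up to 216.
- Enrolled per arm: 216/0.80 = 270, total 540. This matches exactly, so the figure contains no provider term. The age-two inputs give 230 evaluable and 288 enrolled per arm (576), which does not match.

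**Step 2: baseline at the 600 target.** 300 × 0.80 = 240 evaluable per arm. The standard error is 15.65 × √(2/240) = 1.429, the ratio of difference to standard error is 4.888/1.429 = 3.421, and power is Φ(3.421 − 1.960) = 92.8%.

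**Step 3: add providers in the MI arm.**
- Design effect in that arm: DE = 1 + (240/k − 1)ρ.
- Variance inflation of the arm difference: f = (1 + DE)/2.
- Actual level of a test that ignores providers: 2[1 − Φ(1.960/√f)].
- Power of a test that uses the correct standard error: Φ(3.421/√f − 1.960).

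| ρ | k | DE | √f | Actual level | Power |
|---|---|---|---|---|---|
| 0 | any | 1.00 | 1.000 | 5.0% | 92.8% |
| 0.01 | 4 | 1.59 | 1.138 | 8.5% | 85.2% |
| 0.01 | 12 | 1.19 | 1.046 | 6.1% | 90.5% |
| 0.02 | 4 | 2.18 | 1.261 | 12.0% | 77.4% |
| 0.02 | 6 | 1.78 | 1.179 | 9.6% | 82.7% |
| 0.02 | 12 | 1.38 | 1.091 | 7.2% | 88.0% |
| 0.05 | 4 | 3.95 | 1.573 | 21.3% | 58.5% |
| 0.05 | 12 | 1.95 | 1.215 | 10.7% | 80.4% |

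Coverage of the nominal 95% interval for the average effect over providers is 100% minus the actual level; at ρ = 0.02 it is about 88% to 93%.

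**Step 4: what each ρ means in surfaces.** The between-provider SD is √ρ × 15.65: 1.6 surfaces at 0.01, 2.2 at 0.02 and 3.5 at 0.05. These are 32%, 45% and 72% of the assumed effect of 4.888.

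The formulas use normal quantiles and equal caseloads. Few providers or unequal caseloads would make the loss larger.

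**The case against.** The strongest reply is that the article does not exclude a provider term. It commits to mixed models and leaves the covariance structure open; a provider random effect fits within that, and an analysis plan that is not shown may contain one. This stands to the extent that the model cannot be called fixed against providers. But the text frames that structure around repeated measures over time, and the plots it lists would not reveal a provider component. Nor does the reply touch the sample size, which is a stated calculation without such a term.

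A reader might infer more than the document supports:
- **That the standard errors are too small as a matter of fact.** This needs a provider ICC above zero, which is not given. Common training, a script and feedback are meant to keep it low, and Step 4 shows that 0.05 is a large spread.
- **That there are only a few providers.** No number appears, and the Discussion says that more local staff were hired, without giving their roles.
- **That MI children are strictly nested in providers and control children are not.** Continuity is intended only where possible, and the staff for control visits are not described.
- **That type I error is inflated in any case.** If MI has no effect with any provider, there is no treatment-induced provider variation and no inflation. Inflation arises when provider effects differ around a zero average. Interval coverage, however, suffers whenever they differ, if the inference is meant to reach beyond these particular providers.

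The rise to 600 also helps: at ICC 0.01 with 12 providers, power is still about 90%. At 0.02 or above it does not reach 90% anywhere in the range of 4 to 12.

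**Conclusion.** The concern holds in conditional form. The sample size contains no allowance for providers, and the described analysis names only correlation within the child, while the protocol intends provider continuity in the MI arm. The consequence ranges from none at ICC 0 to a serious loss at ICC 0.05 with four providers; the middle case of six providers and ICC 0.02 gives an actual level of 9.6% and power of 82.7%. These sizes rest on assumed provider numbers and ICCs, equal caseloads and clustering in the MI arm alone. They show what the plan is exposed to and do not estimate what will happen.

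**What to change.** Before analysis begins:
1. Confirm that the provider is recorded at every MI visit. The MI section's list of recorded items does not include it, although fidelity feedback implies that audited sessions can be traced to a provider.
2. State the number of providers and who conducts the control visits.
3. Prespecify a provider random effect in the MI arm, and in the control arm too if identifiable providers deliver those visits. Use Kenward-Roger or Satterthwaite degrees of freedom, and assign each child to the provider of most of its visits.
4. Restate power at 600 for a range of provider ICCs, without enrolling more.

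The cost is one data field to confirm, one model term and a short power table. The downside is a somewhat wider interval when providers are few. If the provider variance is estimated at zero, the fitted model reduces to the one without that term.

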## Discussion

As perhaps the first randomized controlled trial of an MI behavioral intervention for ECC in an AI population, the design of this research protocol has involved complex adaptations of behavioral strategies and attention to issues related to acceptability of assessments, interventions, strategies, and procedures.

Major issues for the study were addressed with deliberate community involvement, according to community based participatory research methodology. Presenting issues, seeking feedback and strategizing about solutions as a team empowers and supports the community in seeking sustainable solutions to oral health issues, and establishes trust in the research mechanism. In addition to the biannual Community Advisory Board (CAB) meeting, community members are directly represented as hired staff in the field. The CAB advised our development team on communication norms for the tribe and the design features of all specifically created materials which reflect tribal colors, symbols, and distinguish the materials as being created for this oral health project and this tribe.

This behavioral trial is unusual in two respects. First, it provides enhanced community services to the control group. In this way, we provide some level of community service to everyone participating in the study. Our experience in working with tribal groups made it clear that they would not be comfortable with the absence of services for a control group. Second, the use of MI for behavior change in caries reduction in the intervention is unique in itself and the study will provide a model for aspects of MI implementation, such as desirable characteristics of intervention providers, individual adaptation of the approach, and fidelity assurance.

Challenges to recruitment and retention, which is defined as successful completion of the required study visits, and our approaches to resolving those may also be instructive for future study or implementation of behavioral strategies for oral health. Working on a reservation with a low income, rural and mobile population has its own complexities. Isolated communities and difficult commutes to reach the participant make it harder to recruit and retain participants. Recruitment was not meeting the target in the first year, therefore new recruitment strategies were introduced, such as extending recruitment to nearby areas off the reservation (as the population is mobile) and reaching out to all local programs which provide for maternal and child health. Other strategies include advertisements and public service announcements on local radio stations and flyers posted in public areas and advertisements in area newspapers. As the project increased in number of participants and became known in the local community, we were able to hire more staff from the local community, which has also helped with recruitment efforts.

The weather has been a factor in this study. Severe winter storms in the region may make travel impossible and result in several days of closure of schools, roads, and services annually. Our study follows the local school closure and road closure policy. In all seasons, even when major roads are open, local village roads may not be cleared, thus neither staff nor participants can travel the impassable miles of snow-packed or muddy dirt roads.

Of the stated three primary aims, two have been completed. With the support of the community, culturally specific materials and public service announcements have been developed and are in use with the study participants and for the benefit of all community members through radio, newspaper, and billboard presentations. The MI manual and materials were developed, pilot tested, and in full study use. The remaining primary aim will be met at the conclusion of the study when all participant children who complete the study have their three dental screenings. Data analysis will commence post conclusion of all data collection. The issue of ECC is endemic on the Pine Ridge Reservation and the problem has existed for decades. An effective and parsimonious methodology is needed to stop the generational repetition observed with ECC. This study should provide robust evidence as to the effectiveness of MI in reducing ECC in the first three years of life in this underserved community. If it is effective in reducing the disease, it could provide a methodology to end the pain and discomfort experienced by many AI children. children as they grow from infancy to school age.

### Ethical considerations and approvals

The trial has been approved by the Oglala Sioux Tribe Research Review Board, the Colorado Multiple Institutional Review Board and the Aberdeen Area Indian Health Service Institutional Review Board. This study is reviewed by a number of oversight groups comprised of the National institute of Dental and Craniofacial Research, External Scientific Advisory Committee, Community Advisory Committee, and Data and Safety Monitoring Board.

## Trial status

The trial is currently enrolling participants.

## Abbreviations

ACASI: Audio computer-assisted self-interviewing; AI: American Indians; AN: Alaska Natives; BRFQ: Basic Research Factor Questionnaire; CAB: Community Advisory Board; dmfs: decayed missing filled surfaces; ECC: early childhood caries; ESC: enhanced community services; IHS: Indian Health Service; MI: motivational interviewing.
